**1. Study title and design**

**1.1 Study title**

Title: **C**hanges of cognitive function in patients with mild to moderate **A**lzheimer’s disease associated with or without white matter lesions after **R**ivastigmin**E** patch th**ER**apy – multi-center, prospective, open-label clinical trial (**CAREER study**)

**1.2 Study design**

Investigator Initiative Trial, Multi-center, Prospective, Open-label

Vascular dementia (VaD), which is the second most common cause of dementia, accounts for about 20% of all dementia cases. Pure VaD is mainly caused by cerebrovascular disease (CVD) or small-vessel disease (SVD), but over 40% of VaD is often mixed with AD pathology [6]. In other words, there is growing evidence that parallel cerebrovascular and neurodegenerative pathology is observed in AD and VaD (mixed AD with cerebrovascular disease). Furthermore, it has been reported that several vascular risk factors play important roles in the development of AD.

Since cholinergic structures, such as the basal forebrain and hippocampal CA1, are vulnerable to ischemic injury and widespread white matter bundles of both lateral and medial cholinergic pathways reach almost all areas of the neocortex, cerebrovascular disease, such as localized stroke or microangiopathy mainly involving white matter may interrupt these cholinergic pathways. Since AD and VaD share the common neurochemical characteristics of cortical cholinergic depletion, AChEIs have been used as the major treatment for pure VaD or mixed AD with CVD, as well as pure AD.

Rivastigmine, which inhibits both acetylcholinesterase and butyrylcholinesterase (BuChE), has previously been shown to be beneficial in preventing neuronal degeneration by increasing regional cerebral blood flowing both AD and VaD. The neuroprotective effects of rivastigmine in the context of ischemic brain conditions have also been observed in animal studies. Thus, rivastigmine may be an important treatment option for AD with concurrent vascular pathology.

In fact, one previous randomized trial has indicated that after rivastigmine treatment for 26 weeks, patients with AD with vascular risk factors (VRFs) had greater clinical benefit in cognition, activities of daily living, and disease severity than those with AD without VRFs. Another recent retrospective analysis of a large international 24-week multicenter randomized double-blind placebo-and active-controlled trial also indicates that VRF status seems to have a great impact on treatment response in AD. In these studies, however, VRFs were determined only using the Modified Hachinski Ischemic Score (HIS) or by assessing the presence or absence of reported VRFs at screening. It thus remains unknown whether patients with AD with VRFs had actual concurrent CVD pathology as assessed using brain magnetic resonance imaging (MRI). Furthermore, there have been no studies on the effects of rivastigmine patch in patients with AD with different degrees of WMH.

We thus investigated the efficacy of rivastigmine patch in patients with mild to moderate AD with minimal versus moderate ischemic WMHs. The treatment effect of rivastigmine is generally larger in patients with AD with VRF than in those with AD without VRF [15], and that VRFs are associated with greater WMHs or reduced white matter integrity [18,19]. We thus hypothesized that patients with AD with moderate WMHs will have greater clinical improvements from baseline than those with AD with minimal WMHs. To maximize the therapeutic effects of rivastigmine on cognitive function, we used a transdermal 9.5 mg/24hour rivastigmine patch (10cm2), which offers continuous delivery of the drug with minimal plasma fluctuations. This delivery method leads to potentially similar efficacy and fewer side effects compared to the highest dose of rivastigmine capsule.

**4. Objectives**

**4.1 Rationale of the study**

We hypothesized that rivastigmine patch will provide benefits to AD patients with white matter changes compared to those without any white matter changes. Possible explanation about favorable benefits for AD with white matter changes is that rivastigmine may act on both Alzheimer’s and vascular pathologies contributing to dementia, providing additive treatment effects in patients suffering from both conditions concurrently. To our Knowledge, there was no study or clinical trial to compare the changes of cognitive function, ADL, BPSD and caregiver burden in two groups of patient with Alzheimer’s disease associated with or without white matter changes after rivastigmine transdermal patch therapy.

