**4.2 Primary objective**

To evaluate and compare the changes of cognitive function (as measured by ADAS-Cog) in the two group of patients with Alzheimer’s disease associated with and without white matter changes after rivastigmine patch therapy

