**6.2.2 Subject assignment and prescribing and administering medication**

Patient subjects will be allocated to AD without white matter change group or AD with white matter change group at the baseline. All patients start on a 5-cm2 patch and their dose is increased to a 10-cm2 patch after 4 weeks. White matter changes will be defined by CREDOS protocol. Periventricular white matter (PWM) changes are classified into P1 (caps or rim <5 mm), P2 (5 mm <caps or rim <10 mm), P3 (10 mm <caps or rim). Likewise, deep white matter (DWM) ischemic lesions are classified into D1 (the longest diameter of DWM lesion <10 mm), D2 (10mm<DWM<25mm), and D3 (25mm <DWM). The patients would be divided into two groups according to combinations of PWM and DWM ischemic lesions: Group I (without or minimal white matter changes: D1P1,) and Group II (mild to moderate white matter changes: D1P2, D2P1, D1-P3, D2-P2, D2-P3, D3-P1, D3-P2).

| **Treatment Arm** | **# of Patients Entered Treatment** | **Type of Study Drug** | **Compound** | **Min Dose** | **Max Dose** | **Frequency** | **Admin. Route** |
| --- | --- | --- | --- | --- | --- | --- | --- |
| AD without WMC | 200 | Exelon patch | Rivastgmine | 5cm2 | 10cm2 | qd | PO |
|  |  |  |  |  |  |
| AD with WMC | 100 | Exelon patch | Rivastgmine | 5cm2 | 10cm2 | qd | PO |
|  |  |  |  |  |  |

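### With every patient on the same patch and no untreated comparator, the planned contrast can compare on-treatment change but cannot establish the hypothesis of greater drug benefit with white matter change

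*Protocol*

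**What the plan says.** Section 4.1 of the protocol gives the hypothesis as "We hypothesized that rivastigmine patch will provide benefits to AD patients with white matter changes compared to those without any white matter changes". As a possible mechanism it suggests that the drug acts on both pathologies, "providing additive treatment effects in patients suffering from both conditions concurrently". The Background (section 3) says that the trial investigates the efficacy of the patch in minimal versus moderate white matter disease. It then words the hypothesis more narrowly: "We thus hypothesized that patients with AD with moderate WMHs will have greater clinical improvements from baseline than those with AD with minimal WMHs".

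Section 1.2 describes the design as "Investigator Initiative Trial, Multi-center, Prospective, Open-label". Under section 6.2.2, "The patients would be divided into two groups according to combinations of PWM and DWM ischemic lesions", and "All patients start on a 5-cm2 patch and their dose is increased to a 10-cm2 patch after 4 weeks". The schedule table in section 6.2.1 is the same for both groups. No placebo arm, untreated arm or external control is described. Section 8.1 compares the changes by ANCOVA and names only the baseline score as covariate.

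The primary objective in section 4.2 is "To evaluate and compare the changes of cognitive function (as measured by ADAS-Cog) in the two group of patients" after patch therapy. Section 8.3.1 defines the primary outcome as ADAS-cog change from baseline at week 24.

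**The concern.** The section 4.1 hypothesis is about effect modification: the drug does more for patients with WMC than for those without. To test it, one needs the drug effect in each group, meaning treated change against the change that would have occurred without treatment. The trial observes only treated change. If the two groups would have followed different courses over 24 weeks untreated, that difference enters the contrast in full.

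The protocol's own reasoning makes a difference in course plausible, since it describes the WMC group as carrying vascular as well as Alzheimer's pathology. Adjustment for the baseline score does not supply the missing untreated course, and no analysis plan could, because the data are not collected.

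At stake is the headline conclusion. If sections 3 and 4.1 guide interpretation, a positive result could be read as greater drug benefit when it shows only different progression. A null result could hide a real difference in drug effect.

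**Working it through.** **The plan's own figure.** Inputs from section 5.3: difference 2.3 points, SD 6.0, two-sided 5%, ratio 1:2. The power is not visible in the text, so 80% is assumed.

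n(WMC) = (1.960 + 0.842)² × 6.0² × (1 + 1/2) / 2.3² = 7.849 × 54 / 5.29 = 80.1, rounded up to 81.

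The other group is 162 and the total 243, as stated. (Powers of 85% and 90% would give 92/184 and 108/216, which do not match.) The sample size is sound for the contrast it serves.

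**What the contrast estimates.** In group k, let τ be the drug effect and ν the untreated 24-week change, both signed so that positive is better. The mean on-treatment change is τ + ν, so

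Group II − Group I = (τ₂ − τ₁) + (ν₂ − ν₁).

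Section 4.1 concerns the first bracket. Sections 4.2 and 8.3.1 concern the sum. Only the sum is observed.

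**Illustration 1: equal drug effect (τ₂ = τ₁).** The gap g = |ν₂ − ν₁| is an assumption, because the documents give no untreated course by WMC status. Evaluable patients are 80/160, which is 80% of the planned 100/200. SE = 6.0 × √(1/80 + 1/160) = 0.822. The noncentrality is g/SE, and rejection is by two-sided 5% t-test.

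| Assumed g (points) | g/SE | Chance of p<0.05 | Of which in the direction opposite to g |
|---|---|---|---|
| 0.5 | 0.61 | 9.3% | 0.5% |
| 1.0 | 1.22 | 22.8% | 0.1% |
| 1.5 | 1.83 | 44.4% | <0.1% |

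At 81/162 the chances are 9.4%, 23.0% and 44.8%. The last column shows why direction matters. If WMC patients decline faster untreated, a significant result favouring them is rarer than the nominal 2.5%. The 9% to 44% figures amount to a false finding of more benefit with WMC only if those patients decline more slowly untreated.

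**Illustration 2: true drug advantage of 2.3 points with WMC, but faster untreated decline by g.** The net difference is 2.3 − g. At 81/162, SE = 6.0 × √(1/81 + 1/162) = 0.816.

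| Assumed g (points) | Net difference | Power |
|---|---|---|
| 0 | 2.3 | 80.1% |
| 0.5 | 1.8 | 59.3% |
| 1.0 | 1.3 | 35.4% |
| 1.5 | 0.8 | 16.4% |

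Both illustrations use the unadjusted t-test on which section 5.3 sizes the trial.

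**The case against.** The strongest reply is that the operative text is already right. The title, the primary and secondary objectives, the primary outcome and the sample size all concern change during treatment in two groups. The Background's own hypothesis sentence also concerns improvement from baseline. This stands. A reader might infer that the primary objective cannot be answered or must be rewritten. The documents do not support that, because sections 4.2 and 8.3.1 state a comparison that this design can make.

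Second, the phrase on additive effects is offered as a possible explanation within a rationale, and no section says that a significant result will be declared as greater drug benefit. This also stands. The phrase is not a rule for drawing conclusions, and how the result will be reported cannot be known from the protocol.

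Third, the gaps are assumed and the rejection rates two-sided. A reader might take 9% to 44% as the rate of false claims in favour of WMC. That holds only under slower untreated decline with WMC, for which the documents give no evidence in either direction.

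Fourth, the loose labels (no WMC at all in section 4.1, minimal versus moderate in the Background) might suggest that the comparison itself is undefined. It is not. Section 6.2.2 fixes the groups by explicit rating combinations, beginning with "Group I (without or minimal white matter changes: D1P1". The labels are a separate wording matter and add no weight here.

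None of this rescues the first sentence of section 4.1 or the efficacy framing in the Background. Both still claim more than a treated-only comparison can show, and the protocol carries no caveat.

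**Conclusion.** The concern holds for the hypothesis in section 4.1 and the efficacy framing in section 3, and no further. It follows from three stated features: one treatment schedule for all, groups formed by a patient characteristic, and no untreated comparator. It does not depend on the assumed numbers.

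Its size does depend on them. Gaps of 0.5 to 1.5 points in untreated course would give a significant group difference in about 9% to 44% of trials with no difference in drug effect. Gaps of the same size in the opposing direction would cut the power for a true 2.3-point advantage from 80% to between 59% and 16%. These rest on SD 6.0, the planned numbers and an inferred 80% design power.

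This should be fixed, but it is a matter of wording and interpretation. The sample size, data collection, test and primary objective are unaffected.

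**What to change.** In section 4.1 and the Background, restate the hypothesis along these lines: *the 24-week change in ADAS-cog during rivastigmine patch treatment differs between Group I (D1P1, no or minimal WMC) and Group II (mild to moderate WMC)*. Drop efficacy and benefit as descriptions of what the group comparison establishes. Add one sentence on interpretation: a difference is an association of WMC with the course on treatment and does not by itself show greater drug benefit. Naming the groups as section 6.2.2 does also settles the labels. The objective in section 4.2 and the outcome in section 8.3.1 need no change.

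The cost is a less favourable permitted claim; no patients or procedures are added.

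For scale, consider testing effect modification directly, with treated and untreated patients 1:1 in each stratum, a 2.3-point interaction and the same SD, alpha and assumed 80% power. That would need 7.849 × 4 × 36 × 1.5 / 5.29 = 320.5, rounded up to 321 with WMC, plus 642 without, or 963 evaluable against the planned 243. Rewording is therefore the proportionate remedy.

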**4.2 Primary objective**

To evaluate and compare the changes of cognitive function (as measured by ADAS-Cog) in the two group of patients with Alzheimer’s disease associated with and without white matter changes after rivastigmine patch therapy

**4.3 Secondary objective**

- To evaluate the change from baseline to week 24 of the following parameters in the two groups of patients with Alzheimer’s disease associated with and without white matter changes after rivastigmine patch therapy

- - MMSE (Mini-Mental State Examination)
  - Frontal Assessment Battery (FAB)
  - Alzheimer’s Disease Cooperative Study - Activities of Daily Living (ADCS-ADL)
  - Caregiver-Administered Neuropsychiatric Inventory (CGA-NPI)
  - Clinical Dementia Rating Scale-Sum of Boxes (CDR-SB)
  - Caregiver burden scale – Korean version of mini- Zarit
  - Adverse events

**5. Study population**

**5.1 Study population**

Probable Alzheimer’s dementia patients

**5.2 Number of subjects**

Three hundred patients

**5.3. Sample size justification**

In order to detect the difference in means of 2.3 (assumed from Kumar et al, 2000 as the difference between patients treated with 6-12 mg/day rivastigmine with and without vascular risk factors) of ADAS-cog change from baseline to Week 24 between AD patients with WMC and AD patients without WMC when a two-group t-test with a 0.05 two-sided significance level is used, the sample sizes in the two groups are 81 in AD patients with WMC and 162 for AD patients without WMC (a total sample size of 243), assuming that the common standard deviation is 6.0 (Winblad et al, 2007; Erkinjuntiti et al, 2002) and the allocation ratio of 1:2. The method of sample size calculation is as follows:

[figure not shown]
,

[figure not shown]

[figure not shown]

[figure not shown]

[figure not shown]

[figure not shown]

[figure not shown]

When the drop-out rate is expected to be 20%, a total number of required will be **300** patients (**100** in AD with WMC and **200** in AD without WMC).

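### Section 5.3: the enrolment total of 300 is rounded down, so 20% drop-out leaves 240 evaluable patients against the stated 243 (minor)

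*Protocol*

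**What the plan says.** Protocol Section 5.3 sets out the inputs. The target effect is given by "In order to detect the difference in means of 2.3" in ADAS-cog change from baseline to Week 24. The spread is given by "assuming that the common standard deviation is 6.0". The test is fixed by "when a two-group t-test with a 0.05 two-sided significance level is used", and the groups are in "the allocation ratio of 1:2", with WMC the smaller. From these the section obtains 81 with WMC and 162 without, "a total sample size of 243".

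It then allows for loss: "When the drop-out rate is expected to be 20%, a total number of required will be" 300, made up of 100 with WMC and 200 without. Section 5.2 repeats the total ("Three hundred patients"), and the treatment table in Section 6.2.2 repeats the 200/100 split.

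The formulas introduced by "The method of sample size calculation is as follows" are figures that do not appear in the text available. The readable text gives no power target.

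**The concern.** The section prints three linked figures: the evaluable number required (243), the expected drop-out (20%) and the number to enrol (300). Any two of them determine the third, and the printed three do not agree. A minimum requirement is normally rounded up. Here the enrolment total has come out below what the requirement and the drop-out rate imply, so at exactly the drop-out the protocol expects, both groups fall short of their stated sizes.

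What is at stake is whether the sample size statement is true as printed. Anyone checking the enrolment target will repeat this one division, and it will not give 300.

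**Working it through.** **Inputs, all from Section 5.3:** difference 2.3; common SD 6.0; two-sided alpha 0.05; two-group t-test; allocation 1:2; drop-out 20%; required 81 + 162 = 243; enrolled 100 + 200 = 300. **Assumption:** power 80%, because no power is stated in the readable text. It fits: the formula below gives 81 in the smaller group at 80%, but 92 at 85% and 108 at 90%.

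**1. Reproduce the base size.** With a larger-to-smaller ratio of 2, the normal formula for the smaller group is

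n = (1 + 1/2) × [SD × (z for alpha + z for power) / difference]²
= 1.5 × [6.0 × (1.960 + 0.842) / 2.3]² = 80.12, rounded up to 81.

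The larger group is 2 × 81 = 162 and the total is 243. The protocol's base figures are reproduced exactly.

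**2. Inflate for drop-out, N/(1 − d).**
- Total: 243 / 0.80 = 303.75
- With WMC: 81 / 0.80 = 101.25
- Without WMC: 162 / 0.80 = 202.5

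The protocol states 300, 100 and 200, each below these values. The common slip of multiplying by (1 + d) would give 243 × 1.20 = 291.6, or 292, so that slip does not explain the 300.

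**3. Work back from 300.**
- 100 × 0.80 = 80 against 81: short by 1
- 200 × 0.80 = 160 against 162: short by 2
- 300 × 0.80 = 240 against 243: short by 3
- Drop-out that 300 covers exactly: 1 − 243/300 = 0.19, or 19%

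**4. Effect on power** (difference 2.3, SD 6.0, two-sided 0.05):

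| Evaluable | t-test (noncentral t) | Normal formula |
| --- | --- | --- |
| 81 / 162 | 80.1% | 80.4% |
| 80 / 160 | 79.6% | 79.9% |

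The loss is about 0.5 percentage points by either method.

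**5. A route that does give 300.** If the unrounded requirement is inflated, 80.12 + 160.24 = 240.36, and 240.36 / 0.80 = 300.45. This is close to 300, with 100.15 and 200.30 by group. It rests on the assumed 80% power, and it may not be the route the sponsor took.

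**The case against.** The strongest reply is that nothing has been miscalculated. The total of 300 is within about 2% of any correctly rounded value. The unrounded requirement divided by 0.80 gives 300.45, so the gap of 3 patients arises only because 80.12 was first rounded up to 81 and doubled. A drop-out rate of 20% is a round planning guess, and half a point of power is far smaller than the uncertainty in the assumed 2.3 and 6.0. This stands as far as the method and the size of the effect go. It does not make the printed statement true: the section itself names 81, 162 and 243 as the sizes required, and 300 with 20% loss does not deliver them.

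A second reply is that drop-outs are not simply lost. Section 8.1 plans an intention-to-treat analysis with last observation carried forward and an ANCOVA on baseline, and Sections 6.2.6 and 7 call for a final assessment of those who stop early. So 79.6% is a planning comparison and not the power of the planned analysis; that also stands. But Section 5.3 chose to inflate for drop-out, and that step should agree with its own inputs. Efficacy is measured only at baseline and at Week 24 or early termination, so a patient without a final assessment has only the baseline score to carry forward. Section 8.1 also plans a per-protocol analysis.

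**Conclusion.** The statement in Section 5.3 is wrong as written, and the defect is minor. With 20% drop-out, 300 enrolled patients leave 240 (80/160), not the required 243 (81/162). The shortfall of 3 patients rests only on figures printed in that section. The power comparison, about 79.6% against 80.1%, rests on the stated difference, SD, alpha and t-test. That 80% was the target is inferred.

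A reader might go further and infer that the drop-out formula was misapplied, or that the trial is underpowered and must enrol more. The documents support neither. The total is consistent with N/(1 − d) up to rounding, the readable text states no power target that is breached, and half a percentage point of planning power does not warrant more patients.

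**What to change.** Keep 300 (100/200) and restate one figure in Section 5.3, in either of two ways:

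- **Change the drop-out rate.** State that 300 allows for 19% drop-out, which leaves 81 and 162 evaluable (100 × 0.81 and 200 × 0.81).
- **Change the evaluable numbers.** Keep 20% and state that it leaves 80 and 160 evaluable (240 in total), with about 79.6% power for the two-group t-test under the stated assumptions.

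The cost is one sentence, and the stated drop-out margin or power becomes very slightly less favourable. Section 5.2 and the table in Section 6.2.2 need no change, because the enrolment figures stay the same. Conduct and analysis are unaffected.

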**5. 4 Inclusion criteria**

1. Age range : 50 – 90 years of age
2. Sex distribution: both men and women. Females of non-childbearing potential or post-menopausal for at least 2 years
3. AD in NINCDS-ADRDA criteria, mild to moderate
4. probable AD with or without mild to moderate whiter matter lesions, excluding multiple large vessel infarcts or a single, strategically placed infarct (angular gyrus, thalamus, basal forebrain, territory of the posterior or anterior cerebral artery) on MRI scan (within 12 months)
5. MMSE score : 10 to 24 at screening
6. Hachinski scores ≤ 4
7. No clinically significant laboratory abnormalities, such as thyroid disease, vitamine B12 deficiency or folic acid deficiency

